### Statistical analysis

For the sample size calculation we used findings from similar studies in comparable populations [24,43,44]. Thus, the number of participants required to detect a standardized difference in cortisol levels of 0.5 between abused women and non-abused controls with 80% power using a cut-off score for statistical significance of 0.05 is 128 (64 per group). Assuming 40% drop out rate before the study ends, around 213 eligible subjects would have to be approached. Assuming 60% response rate we will have to approach approximately 355 women, so 213 would consent to join the study, and of these 128 would be expected to complete the study.

Data will be coded and entered into research database during data collection by the two researchers responsible for recruitment. Stata software will be used for statistical analysis. All data will be checked for expected ranges, presence of outliers and abnormal values.

Sample will be analyzed by comparison of participant exposed to DVA and participants without DVA exposure on the basis of cortisol and mental health state data. Primary study outcome will be reported as diurnal cortisol variation, the degree of decline in cortisol across the day. Secondary study outcomes include CAR, size of post-awakening surge in cortisol that occurs in 30 minutes after awakening and mean salivary cortisol concentration across the day. As an additional measure of tissue cortisol the three saliva samples, awakening, post awakening, and bedtime, will also be assayed for cortisone.

Following descriptive statistics for all the cortisol and mental health outcomes, relationship between them will be investigated using appropriate linear (and, for binary outcomes, logistic) regression models. Using the CAS and CTQ data, these techniques will also be used to investigate the extent to which cortisol measures act as potential mediator between the type, duration and cessation of abuse and mental health condition for this group of women.

Missing data from women who dropped out of the study will be handled first by comparing their baseline variables with those who completed the study, and secondly using imputation techniques [45].

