In addition, the mechanisms through which DVA causes mental and physical conditions are very poorly studied. One mechanism that may contribute to stress-related disorders is the hypothalamic-pituitary-adrenocortical (HPA) axis, which produces cortisol [11-13]. Cortisol activity in healthy children and adults follows a consistent diurnal pattern with peak levels of output observed within the first 30–40 min after awakening followed by a progressive reduction throughout the morning and afternoon with a nadir around midnight [14]. Cortisol levels naturally increase in response to exposure to acute stress and helps organisms cope with a short term homeostatic challenges by modification of metabolic and cognitive function [15]. Chronic stress has the capacity to increase or decrease HPA activity, and the resulting pattern depends, both on features of the stressor and the person facing it. Female survivors describe DVA as traumatic uncontrollable stress that poses a threat to their physical and social self, and is associated with feelings of shame [16]. There are very few studies focused on assessing physiologic correlates of chronic stress in abused women.

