Salivary cortisol has been successfully used as a biological marker of HPA axis activity in epidemiological studies [17,18] including samples of women exposed to DVA [19-21]. Diurnal cortisol slope, cortisol awakening response (CAR), and area under the daytime cortisol curve have been found the most robustly related to psychosocial phenomena and to health outcomes [22]. Systematic review of the endocrine sequelae in chronically stressed but non psychiatric caregivers for family members reveals four studies which reported no difference, five studies reporting increased cortisol output, and four studies reporting hypo- secretion of cortisol compared to controls [23]. Powell et al. [20] have found out that women chronically stressed by undergoing a divorce or separation displayed elevated evening salivary cortisol compared to no stressed women in stable marriages. Moreover, it was the chronic stress rather than depression or acute stress that accounted for the elevation of evening salivary cortisol. Systematic review and meta-analysis of cortisol and posttraumatic stress disorder revealed significantly lower cortisol levels in people with PTSD due to sexual or physical abuse than controls. Interestingly, no difference in cortisol levels was found between controls and people with PTSD due to other types of trauma [24]. In contrast, anxiety disorder was associated with higher awakening cortisol levels [25]. Meta-analysis of studies meeting methodological standards showed that depression was associated with small-to-moderate elevation in cortisol output [26].

Long-term studies are absent in the field of pathophysiology of DVA [22]. The results of existing cross-sectional and short-term longitudinal studies testing the impact of childhood abuse and DVA on women’s HPA axis functioning are contradictory (see Additional file 1).

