Upon completion of questionnaire and anthropometry study participants will be given a saliva sample collection kit that includes a saliva collection device (Salivette tubes) with cotton pledget, an illustrated instruction sheet written in plain language explaining the procedure and providing helpful hints (such as putting the tube next to the bed for morning sample), a saliva collection diary in which participants can record experiences on the day of sample collection and a prepaid packaging addressed to the accredited laboratory compliant with current postal regulations. The participants will be asked to collect three saliva samples as soon as possible after questionnaire survey:

1. Sample 1 “bedtime” – right before getting into bed.

2. Sample 2 “awakening” – next morning as soon as the woman wakes up and is ready to get up for the day.

3. Sample 3 “post-awakening” – 30 minutes after taking awakening sample.

Saliva will be collected by either passive drooling into the tube or by chewing (for 2 minutes) the cotton pledget provided with each tube. Participants must have waited at least 30 minutes after smoking, consuming any food or drink or teeth brushing before collecting the saliva sample. Tubes will be labeled with patient identifier and returned to the laboratory by post or via collection by the researcher. Upon arrival to the laboratory tubes with saliva will be centrifuged to remove the upper saliva layer for subsequent measurement of cortisol. The primary tube including the cotton pledget with individual cells will be then discarded in routine clinical waste. The upper saliva layer will be frozen until analysis. The saliva samples will be analyzed in the Department of Clinical Biochemistry at the Bristol Royal Infirmary using Ultra performance liquid chromatography – tandem mass spectrometry (UPLC-MSMS). The analysis also simultaneously measures cortisone a metabolite of cortisol as an additional measure of circulating cortisol [41,42].

To collect data on known covariates that have been related to diurnal cortisol secretion participants will complete saliva collection diary [22]. Data collected on the day of saliva sampling include: schedule (whether weekend vs. weekday), time of awakening, lifestyle (smoking, alcohol use, caffeine, exercise/activity level, perceived stress and negative mood, recent meal, medications) and menstrual timing.

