## Discussion

The current study: (1) evaluates levels of stress, mental health, and stress biomarker salivary cortisol for currently and recently abused women and non-abused controls, across three time periods over 6 months; (2) explores whether there are altered diurnal patterns of cortisol secretion within this sample; and (3) identifies socio-demographic, abuse and mental health predictors of diurnal cortisol parameters. The study protocol and participant documentation have been amended based on guidance from our research advisory group (five former SURVIVE users) and the pilot study. This study is methodologically strong compared to very few neuroendocrinological studies previously conducted in abused women. Firstly we use three-point saliva sampling protocol across three time periods over 6 months which enables us to obtain the key diurnal cortisol parameters prospectively – the diurnal cortisol slope, the size of awakening response, and the average cortisol exposure across the day. Secondly we shall collect data on a number covariates related to diurnal cortisol secretion in order to control neuroendocrine variables for potential confounding. Thirdly UPLC-MSMS will be used to measure salivary cortisol. UPLC-MSMS is a superior technique to traditional immunoassay steroid methods, with improved sensitivity and specificity which is able to measure both salivary cortisol and cortisone (cortisol metabolite) in the samples simultaneously. Fourthly to measure stress, mental health and abuse we use international validated questionnaires. Finally our targeted sample size is larger than those reported in earlier studies in women exposed to DVA which allows performance of subgroup analysis stratified by mental health status, and characteristics of DVA.

This study should add significantly to our understanding of the physiological mechanisms of DVA and explain causal pathway between abuse and mental health consequences in female survivors. It will improve understanding of neuroendocrine markers associated with abuse and mental health status, potentially leading to studies of prognosis and more targeted management of women who have experienced DVA and its sequelae. Ultimately it might be possible to better target intervention for women experiencing DVA with and without specific mental health sequelae in relation to activity of HPA axis. The current study represents a step on this direction.

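### The three-sample cortisol mean is weighted to the first half hour after waking and cannot be read as average exposure across the day

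*Protocol article*

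**What the plan says.** In the protocol article, Measurements fixes the sampling. Sample 1 is taken "right before getting into bed", sample 2 "next morning as soon as the woman wakes up and is ready to get up for the day", and sample 3 "30 minutes after taking awakening sample". No other saliva is collected at an assessment. The bedtime sample thus comes from the evening before the two morning samples.

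The Background describes the expected pattern as "peak levels of output observed within the first 30–40 min after awakening followed by a progressive reduction", reaching its low point around midnight.

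Statistical analysis makes diurnal variation the primary outcome. The secondary outcomes are the awakening response (CAR) and "mean salivary cortisol concentration across the day". No formula or weighting is given for the mean. Objective 1 lists mean cortisol concentration among its three key parameters. The Discussion presents the three-point scheme as the study's first methodological strength, saying that it provides "the average cortisol exposure across the day".

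The Background also reports that the diurnal slope, the CAR and "area under the daytime cortisol curve have been found the most robustly related to psychosocial phenomena". The area measure is not among the outcomes in Statistical analysis.

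**The concern.** The sampling times and the interpretation placed on the mean do not fit each other. Two of the three samples sit on the rise to the peak or at it. One stands for the evening, and none covers the long decline between.

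The study hypothesis is that abused women have an altered diurnal rhythm, so the shape of the curve may differ between groups. A summary that leans on the morning then mixes shape with total output. A lower mean could be reported as hyposecretion in abused women when output over the waking day is unchanged or raised. The Background describes a literature that already disagrees on direction, so an ambiguous direction bears on the study's own question.

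**Working it through.** **Plan's own figures.** The article gives no numerical value for this outcome. Its sample size (standardised difference 0.5, 80% power, 0.05 taken as two-sided) reproduces: the t-test calculation gives 63.8, so 64 per group and 128 in total; 128/0.6 = 213.3 and 213/0.6 = 355. None of this depends on the point below.

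**Inputs.** From the documents: samples at waking (w), +30 minutes (p) and bedtime (b). Assumed, because the article gives neither: a waking day of T = 16 h (range 14 to 18 h) and all cortisol values, in nmol/L.

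**Formulas.**
- Plain mean: (w + p + b)/3.
- Time-weighted, straight line from +30 minutes to bedtime: [0.5(w + p)/2 + (T − 0.5)(p + b)/2]/T.
- Time-weighted, log-linear decline: [0.5(w + p)/2 + (T − 0.5)(p − b)/ln(p/b)]/T.

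**Weights at T = 16.** The plain mean puts 2/3 = 67% of its weight on samples from a window of 0.5/16 = 3.1% of the day (2.8% at 18 h, 3.6% at 14 h). The straight-line weights are:
- waking 0.25/16 = 1.6%
- +30 minutes (0.25 + 7.75)/16 = 50.0%
- bedtime 7.75/16 = 48.4%

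**Can the direction differ?** Each row compares a reference profile with a flatter one (w/p/b), at T = 16.

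| Reference → flatter | Plain mean | Straight line | Log-linear |
|---|---|---|---|
| 10/15/2 → 8/12/4 | 9.00 → 8.00 | 8.63 → 8.06 | 6.64 → 7.37 |
| 10/15/2 → 8/12/3 | 9.00 → 7.67 | 8.63 → 7.58 | 6.64 → 6.60 |
| 10/15/1.5 → 8/13/4.5 | 8.83 → 8.50 | 8.38 → 8.80 | 6.07 → 8.09 |
| 10/15/1.5 → 9/12/3.5 | 8.83 → 8.17 | 8.38 → 7.84 | 6.07 → 7.01 |

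First row, log-linear: [6.25 + 15.5 × 13/ln 7.5]/16 = 6.64 and [5 + 15.5 × 8/ln 3]/16 = 7.37. The plain mean falls 11%. The log-linear measure rises 11% (also about 11% at 14 and 18 h), and the straight-line measure falls 6.5%.

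- Row 2: the plain mean falls 15% while log-linear exposure is almost unchanged.
- Row 3: the direction reverses under both interpolations.
- Row 4: it reverses only under log-linear decline.

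**General condition (straight line, T = 16).** Suppose waking falls by dw, +30 minutes falls by dp and bedtime rises by db. The plain mean falls when db < dw + dp. The time-weighted mean rises when 7.75·db > 8·dp + 0.25·dw, that is db > 1.03·dp + 0.03·dw. Reversal lies between these bounds.

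**How often on a grid.** Around 10/15/1.5, take equal falls in both morning samples of 0.25 to 4 and bedtime rises of 0.25 to 4, in steps of 0.25 (256 combinations). The direction reverses in 22% under the straight line and 62.5% under log-linear decline. These are shares of an assumed grid, not probabilities.

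**The case against.** **No formula is stated.** The article does not say that the mean is unweighted, and derivation of a secondary outcome is commonly left to the analysis plan, which is not shown. This stands: the two-thirds weight is the plain reading only. But a different formula would not rescue the label. Time weighting removes the double morning weight, yet puts half the weight on the single +30-minute sample (straight line) or relies on a curve across about 15.5 unsampled hours. It also joins a bedtime sample to morning samples from the following day.

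**The reversal rests on assumptions.** This also stands. Cortisol values, day length and decline shape are all assumed, no standard deviation is available to relate an 11% shift to inference, and the time-weighted figures are not observed truth either. A reader might infer that the mean will point the wrong way; the calculation shows only that it can.

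**Other stronger readings that the article does not support.**
- That it predicts raised evening cortisol in abused women. The Background reports that finding for women undergoing divorce or separation, alongside lower cortisol in PTSD after sexual or physical abuse. The study hypothesis gives no direction.
- That the mean largely duplicates the CAR. The CAR is p − w and the mean is a sum; the contrasts (−1, 1, 0) and (1, 1, 1) are orthogonal, so raising all three samples equally moves the mean and leaves the CAR alone.
- That the outcome must be replaced by a log-linear area under the curve. That is one debatable choice, with the two-day problem above.

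**The primary outcome covers flattening.** True, and it limits the harm: a false conclusion on total output requires reading the mean apart from the slope. The Discussion invites that reading by listing average exposure as a separate quantity the scheme delivers.

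**Conclusion.** The point holds, with limited reach. The sampling scheme does not support describing the mean as exposure across the day: two of three samples lie within 30 minutes of waking and the rest of the waking day is unobserved until bedtime. That follows from the stated sampling times and does not depend on any assumed cortisol value. The 67% weight on about 3% of the day rests on the unweighted reading and a 16-hour day; the 3% changes little between 14 and 18 hours.

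The possible disagreement in direction between this mean and time-weighted exposure is shown arithmetically for a flatter rhythm. It is conditional on the assumed values and decline shape. One secondary outcome and its interpretation are affected; the primary outcome and the sample size are not.

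**What to change.** In Statistical analysis, name the outcome the mean of the three samples and state that it is morning-weighted. In the Discussion, withdraw the claim of average exposure across the day. Add that a group difference in this mean will not be interpreted as hyper- or hyposecretion over the day without the bedtime level and the slope beside it.

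Optionally, add a time-weighted summary as a sensitivity analysis, using recorded clock times. State the interpolation assumption, that nothing is observed between the +30-minute sample and bedtime, and that the bedtime sample is from the previous evening. The diary items listed in Measurements include time of awakening but not the time of the bedtime sample, so that entry would be added if the full diary lacks it.

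The cost is a change of wording and, for the option, possibly one diary entry. No extra samples or participants are needed. The downside is a less ambitious description of one secondary outcome.

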## Abstract

**Background:**

Domestic violence and abuse is threatening behavior, violence/abuse used by one person to control the other within an intimate or family-type relationship. Women experience more severe physical and sexual domestic violence and abuse and more mental health consequences than men. The current study aims at exploring of the role of hypothalamic-pituitary-adrenocortical axis activity in abuse impact on women's mental health. Study objectives: 1) To evaluate diurnal cortisol slope, cortisol awakening response, and the mean cortisol concentration in women with a current or recent experience of abuse; 2) To estimate whether cortisol secretion is associated with type, severity, duration and cessation of abuse; 3) To investigate whether cortisol acts as mediator between abuse and mental health condition; 4) To examine whether there is any distinction in cortisol levels between those women exposed to both childhood abuse and domestic violence and abuse and those experienced only the latter. 4) To explore whether cortisol secretion differs between women living in refuge and those still living in the community.

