**Methods/Design:**

To meet study objectives 128 women will be recruited in a domestic violence agency and local communities. Baseline and 3-month follow-up measures will be taken over 6 months after recruitment. Each assessment will include: (1) standardized self-administered questionnaires to evaluate socio-demographics, experience of violence and abuse, mental and physical health; (2) weight and height measurement; (3) self-completion of wakening, post-wakening and evening saliva samples. Saliva will be analysed for cortisol and cortisone using Ultra performance liquid chromatography – tandem mass spectrometry.

We will compare diurnal cortisol parameters between non-abused controls and abuse survivors with and without mental health conditions. First following descriptive statistics for all the cortisol and mental health outcomes, relationships between them will be investigated using appropriate regression models. Second, these techniques will be used to investigate the extent to which cortisol measures act as potential mediators between type, severity, duration of abuse and mental disorders.

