It is evident that most investigators have reported different patterns of alterations in diurnal cortisol output in women exposed to childhood abuse (CHA) and DVA. However there are researchers who have concluded that cortisol is a marker of abuse exposure rather than mental health diagnosis [27,28]; others stated that alteration in cortisol output is a correlate of abuse-related mental disorder [29,30]. Currently, it is known that CHA influences the psychobiology of cortisol function and that there is a development from hyper secretion of cortisol to hypo secretion by early adulthood [14]. It is also known that both physical and psychological DVA have significant impacts on the neuroendocrine system of women [27]. At the same time it is not clear whether currently and recently abused women, who have abnormal diurnal cortisol profiles, demonstrate poorer mental health outcomes and how this may correlate with type, severity, duration and cessation of abuse. There is a hypothesis that DVA survivors may be characterized by alterations in HPA axis activity [31] and that further longitudinal studies are needed to identify specific stress system disturbances in this group [2,32]. The current research study aims to investigate the role of the HPA axis on the impact of DVA on women’s mental health. This study tests the hypothesis that compared to non-abused controls all abused women have altered diurnal rhythm in cortisol secretion and that the pattern of this alteration is predicted by abuse characteristics, such as its type, severity, duration, and cessation.

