### Study objectives

1. To evaluate the key diurnal cortisol parameters (diurnal cortisol variation, CAR, and mean cortisol concentration) in women with a current or recent experience of DVA

2. To estimate whether cortisol parameters are associated with type, severity, duration and cessation of abuse

3. To investigate whether cortisol outcomes act as a mediator between the features of abuse and mental health state

4. To examine whether there is any distinction in cortisol levels between those women exposed to both CHA and DVA and those experienced only the latter

5. To explore whether cortisol secretion differs between women, living in a domestic violence refuge and those still living in the community (after adjustment for confounding effects of abuse severity and continuing contact with abuser).

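### Every stated mediation model takes features of abuse as the exposure, so none estimates whether cortisol carries the effect of abuse itself (abused versus control) on mental health

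*Protocol article*

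**What the plan says.** The Protocol article words the mediation question in two ways.

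**As a question about abuse.** The Background section states: "The current research study aims to investigate the role of the HPA axis on the impact of DVA on women’s mental health". Objective 3 in the abstract reads: "To investigate whether cortisol acts as mediator between abuse and mental health condition". The Discussion expects the study to help explain the causal route from abuse to mental health consequences.

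**As a question about features of abuse.** Objective 3 under Study objectives reads: "To investigate whether cortisol outcomes act as a mediator between the features of abuse and mental health state". The abstract's Methods/Design paragraph will examine "the extent to which cortisol measures act as potential mediators between type, severity, duration of abuse and mental disorders". The Statistical analysis section names the data and the regression approach ("Using the CAS and CTQ data, these techniques will also be used to investigate the extent") and then the exposures and population: "cortisol measures act as potential mediator between the type, duration and cessation of abuse and mental health condition for this group of women".

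The Statistical analysis section also plans a comparison of exposed and unexposed women on both cortisol and mental health, and regressions relating cortisol to mental health. The sample size, 128 women (64 per group), is set for a 0.5 SD difference in cortisol between abused women and controls.

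**The concern.** Whether cortisol carries the effect of abuse and whether it carries differences among abused women are separate questions. The first needs unexposed women in the model. The second can be answered without them, and its answer does not settle the first.

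The distinction matters here because the Background section hypothesises altered cortisol rhythm in all abused women compared with controls. If cortisol shifts in every abused woman to a similar degree, features of abuse will not predict it, and a features-only mediation will be null even where cortisol carries much of the effect of abuse. A reader of the abstract's objective could then take that null as evidence against cortisol as a mechanism.

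The article fixes the mediation exposure itself and fixes it differently in different places, so this is not simply detail left to a fuller plan.

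**Working it through.** **1. Mediation exposures side by side (Protocol article)**

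| Place | Exposure | Population |
|---|---|---|
| Abstract, objective 3 | abuse, unqualified | not stated |
| Background, aim | impact of DVA (no mediation model named) | not stated |
| Study objectives, objective 3 | features of abuse | not stated |
| Abstract, Methods/Design | type, severity, duration | not stated |
| Statistical analysis | type, duration, cessation | an undefined group of women |

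No row gives abused versus control as the exposure of a mediation model. Severity is in the abstract's list but not in Statistical analysis; cessation is the reverse.

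**2. Who can enter the model**

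Under Measurements, the added duration item starts at a single occasion and lists no category for none. Cessation presupposes abuse. Neither has a natural value in a never-abused control. Type and severity differ: the CAS sums 30 items scored 0–5, so an unexposed woman has a valid score of zero, and a control can have any CTQ score. The abused-only reading is therefore the most natural one, but it is an inference.

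**3. What the other planned analyses give**

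Write a for the effect of exposure on cortisol and b for the effect of cortisol on symptoms given exposure. The indirect effect is a × b.

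- The group comparison on cortisol gives a.
- The group comparison on mental health gives the total effect.
- The cortisol–mental health regressions give something close to b, but are not stated to adjust for exposure group.

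No stated step forms a × b for abused versus control.

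**4. Why a null features model is not informative about abuse**

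Take the sample-size difference of 0.5 SD as a uniform shift in all abused women, and assume b = 0.2, 0.3 or 0.4 SD of symptoms per SD of cortisol (the article gives no value).

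- Abused versus control: 0.5 × 0.2 = 0.10, 0.5 × 0.3 = 0.15, 0.5 × 0.4 = 0.20 SD.
- Within abused women: a = 0, so a × b = 0 for every b.

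**5. The plan's own figure**

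Two-sample t-test, d = 0.5, two-sided 0.05, 80% power: 63.8, so 64 per group and 128 in total, with power 80.1% at 64 per group. The stated 128 reproduces. With 40% dropout, 128 / 0.6 = 213.3, against the stated 213.

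**6. Illustrative precision**

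On the abused-only reading, 64 / 128 = 50% of planned completers enter. The smallest correlation detectable on a single path with 80% power is tanh((1.96 + 0.84) / √(n − 3)): 0.34 at n = 64 and 0.25 at n = 128.

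Joint-significance power is approximated as power(a) × power(b), treating the tests as independent, with power for a correlation r taken as Φ(atanh(r)·√(n − 3) − 1.96). The 0.5 SD difference as a correlation is 0.5 / √(0.25 + 4) = 0.24, so r = 0.25 is used for the continuous exposures. The values of b, treated here as partial correlations, are assumptions.

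| Exposure and sample | b = 0.2 | b = 0.3 | b = 0.4 |
|---|---|---|---|
| Abused v control, n = 128 (a: 0.801) | 50% | 75% | 80% |
| CAS score, controls included, n = 128 (a: 0.815) | 51% | 76% | 81% |
| Feature, abused only, n = 64 (a: 0.514) | 18% | 35% | 47% |

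For example, at b = 0.3: 0.801 × 0.933 = 0.75 for the group contrast, and 0.514 × 0.676 = 0.35 for the abused-only model. The second row shows that the gap comes from the number of women, not from the choice between group and score.

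**The case against.** The strongest reply is that the body of the article is consistent. Objective 3 under Study objectives concerns features of abuse, and the Statistical analysis section analyses features of abuse. On that view the abstract's word abuse is shorthand, the Background aim is broad and names no mediation exposure, and the choice of exposures and subsets can be left to a fuller plan. The Background hypothesis also has a second part, that abuse characteristics predict the pattern of alteration, which the features analysis serves directly.

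Much of this stands. Features-based mediation is a legitimate question, and whether it or the group contrast comes first is a preference. Three stronger readings that a reader might infer are not supported:

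- **That the aim is never tested.** The article compares exposed and unexposed women on both cortisol and mental health and relates cortisol to mental health. Only the indirect effect for abused versus control is absent.
- **That half the sample is discarded.** Controls serve the primary comparison. Their exclusion from the mediation is inferred from an undefined phrase, and the CAS and CTQ data named for that analysis can exist in controls.
- **That mediation power falls by a known amount.** The article gives no mediation path sizes, and n = 64 depends on the abused-only reading and on counting 6-month completers only.

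The reply does not remove the core: no stated model matches the abstract's objective 3, the population is undefined, and the two lists of features disagree.

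**Conclusion.** The point holds as a mismatch between question and model. The abstract's objective 3, the aim in Background and the Discussion concern the effect of abuse; every stated mediation analysis uses features of abuse, most naturally within abused women. The abused-versus-control indirect effect has no stated model, and a null features-only result could not stand in for it.

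The uniform-shift example is a limiting case. If features do predict cortisol, the within-abused analysis is informative about those features, but still not about abuse versus no abuse. The power figures are illustrative only: they rest on assumed path sizes, independent tests and, for n = 64, the abused-only reading. The sample size of 128 is not in dispute. This is a cheap improvement that lets the study answer its own aim, not a flaw in the primary comparison.

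**What to change.** - Add one whole-sample mediation model with DVA exposure as the exposure, either abused versus control or CAS score with controls included. Regress cortisol on exposure, then symptom score on exposure and cortisol, and report the indirect effect with an interval. Use the same confounder adjustment as the primary comparison.
- Keep the features-of-abuse mediation as the analysis within abused women.
- State which women enter each model, replacing the undefined group in Statistical analysis.
- Align objective 3 and the Methods/Design paragraph in the abstract, objective 3 under Study objectives, and Statistical analysis. Decide whether severity and cessation belong in the list and use one list throughout.
- Report a null features result as concerning differences among abused women only.

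The cost is one extra set of regressions; no new measurements are needed, since cortisol and mental health are already to be compared in both groups. The drawback is that the group contrast comes from a convenience sample with friend and community controls, so the indirect effect carries that contrast's confounding as well as any confounding between cortisol and symptoms, and should be reported with that caution.
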